### Blinding

All patients and clinical staff clinical outcomes will remain blinded to the treatment group. It is not possible to blind observers recording radiological outcomes as different implant designs will be used within each treatment group. Both conventional manual instrumentation and robotic-arm-assisted surgery are only compatible with implants from their respective manufacturers, and so identical implant designs could not be used in both treatment groups. Study patients will be identifiable with a unique study number. Only the research physiotherapist will have the key to identify individual patients and their respective treatment arm. Any documents related to the study will be archived directly at the study site by the research physiotherapist within a locked filing cabinet in a locked research office. This office has swipe card access with onsite security and 24-h CCTV surveillance. Patient data will be logged electronically using each patient’s unique identification number with computer software on an encrypted, password-protected research computer.

### Sample size

Using the study by Bell et al. assessing differences in accuracy of component positioning between conventional and robotic UKA, the mean difference in femoral sagittal component positioning was set at 2° and standard deviation assumed at 4° [4]. Using a two-tailed, two-sample *t* test with a power of 80% (1–β), significance level of 5%, and an effect size of 0.5, this study required 128 patients to detect this minimum difference between the two treatment groups. To account for 10% attrition in the sample size during follow-up, the sample size was set at 140 patients.

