### Statistical analysis

The analysis of the per-protocol population will be considered the primary analysis. The differences between the CO UKA and RO UKA groups will be analysed by calculating the difference from baseline, per patient, and a two-sided confidence interval for the difference between the changes from baseline values will be calculated. This confidence interval will cover the true difference in the percentage change from baseline with a probability of 95%. The following statistical methods will be employed to analyse the data: descriptive statistics, independent *t* test, paired *t* test, analysis of variance, Fisher’s exact test, chi-square test, and graphical displays. Assumptions of normality will be tested with the D’Agostino test. Assumptions of homogeneity of variance will be tested with Levene’s test. If the distributional assumptions are (severely) violated, non-parametric techniques, such as Mann-Whitney’s test, will be employed. In the event that RO UKA is converted to CO UKA intraoperatively, analysis will be performed using the intention-to-treat population and the treatment actually received by the patients. Intraoperative conversion from RO UKA to CO UKA will be documented and presented and published as part of the study. The Bonferroni correction will be used to determine the level of significance due to multiple comparisons of secondary outcomes. Statistical significance is set at a *p* value < 0.05 for all analyses, and all statistical analysis will be performed using SPSS software version 26 (SPSS Inc., Chicago, IL, USA).

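### Minor inflation slip: 140 patients cover 8.6% loss from the required 128, not the stated 10%

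*Protocol article*

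**What the plan says.** In the Sample size section of the protocol article, "the mean difference in femoral sagittal component positioning was set at 2° and standard deviation assumed at 4" degrees, which gives "an effect size of 0.5". The test, power and alpha are also given: "Using a two-tailed, two-sample *t* test with a power of 80% (1–β), significance level of 5" per cent. From these the section derives a requirement of 128 patients, and it adds: "To account for 10% attrition in the sample size during follow-up, the sample size was set at 140 patients".

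Four other places bear on the point:

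- **Outcomes:** the primary outcome, accuracy of implant positioning, is read on a postoperative CT at 6 weeks.
- **Trial design:** follow-up lasts 2 years.
- **End of protocol treatment:** data collected before a patient discontinues are kept for analysis.
- **Statistical analysis:** "The analysis of the per-protocol population will be considered the primary analysis".

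**The concern.** The section prints a required number, an attrition rate and a total, so a reader can check one against the others. Taking 10% off the total gives fewer patients than the requirement. The sample size statement therefore claims a little more protection against missing outcomes than the trial has.

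What is at stake is the accuracy of a stated design figure. The sentence should say how much loss 140 patients can absorb, and at which time point that loss counts. The article prints all three numbers, so this is not a detail left to a fuller document.

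**Working it through.** **Inputs (Sample size section).** Difference 2°, SD 4°, two-sided two-sample t test, alpha 0.05, power 80%, attrition 10%, total 140. Allocation is 1:1 (Abstract), and equal arms are assumed throughout.

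**Step 1. Reproduce 128.** The effect size is d = 2/4 = 0.5. With n per arm, the t statistic has 2n − 2 degrees of freedom and noncentrality d × √(n/2). Solving for 80% power gives n = 63.77, so 64 per arm and 128 in total. At n = 64 the noncentrality is 0.5 × √32 = 2.83 and power is 80.1%. The stated 128 reproduces exactly.

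**Step 2. Check the inflation.**

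| Calculation | Result |
|---|---|
| Left after 10% loss from 140 | 140 × 0.90 = 126 (2 below 128) |
| Needed so that 128 remain after 10% loss | 128/0.90 = 142.2, so 143 (144 for equal arms) |
| Shortcut of adding 10% | 128 × 1.10 = 140.8, so 141 |

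Rounded up, neither method of inflating 128 by 10% gives 140.

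**Step 3. Loss that 140 covers.** 140 − 128 = 12 patients, and 1 − 128/140 = 0.0857, or 8.6%. A 10% loss is 14 patients.

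**Step 4. Power if the full 10% lack the primary outcome.** With 63 per arm the noncentrality is 0.5 × √31.5 = 2.81 on 124 degrees of freedom, and power is 79.5%. That is 0.5 points below 80% and 0.6 points below the 80.1% at 128.

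**Step 5. Cross-check by the normal approximation.** This method needs 63 per arm, or 126 in total, with power 80.1%. Also 126/0.90 = 140. The total of 140 would thus be exact for a requirement of 126, but the article states 128 and names the t test.

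**Step 6. Illustration only: further exclusions under the per-protocol analysis.** The article gives no exclusion rate, so the totals below are assumed.

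| Evaluable patients (assumed) | Total loss from 140 | Power (t test) |
|---|---|---|
| 120 | 14% | 77.5% |
| 112 | 20% | 74.6% |
| 105 | 25% | 71.8% |

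**The case against.** **The effect is at rounding level.** A power of 79.5% rounds to 80%, and half a point is well within the uncertainty of an assumed SD. By the normal approximation 126 patients suffice and 140 is the exact inflation. The point about size stands. The approximation does not rescue the sentence, because the section names the t test and states 128, and that number comes from the t test.

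**The loss may not reach the primary outcome.** The 10% is given for follow-up, which lasts 2 years, while the primary CT is at 6 weeks. Data up to discontinuation are used, so a patient who has had that CT and leaves later still has a primary outcome. This stands, and it limits the conclusion: the article gives no loss rate for 6 weeks, so a shortfall in the primary analysis is possible but not shown.

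**Two stronger readings are tempting.** A reader might infer that the trial simply misses its stated power. The document does not support that, since the stated power is met whenever 8.6% or fewer lack the primary outcome. A reader might also infer that the per-protocol primary analysis makes the gap materially worse. The 10% is indeed described only as attrition, so such exclusions would come on top of it. But the article states no exclusion rate and does not define the set. The one departure it discusses, intraoperative conversion from robotic to conventional surgery, is to be analysed by intention to treat and by treatment received; nothing says those patients are dropped. The figures in Step 6 are therefore only a sensitivity range.

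**Conclusion.** The attrition sentence is wrong as written, by a small amount. On the protocol's own method, 140 patients cover 8.6% loss and not 10%. The shortfall is 2 evaluable patients, or 3 to 4 enrolled. If the full 10% lacked the primary outcome, power would be 79.5% against the stated 80%.

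This rests on the stated 2° difference and 4° SD, equal arms, and the t test that the section names. It is a correction to a stated figure. It does not show that the trial is underpowered, and it gives no reason to change the design.

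**What to change.** Keep 140 and replace the attrition sentence with wording such as: *140 patients keep 80% power with up to 8.6% lacking a usable 6-week CT in the primary analysis; at 10% loss power is 79.5%.* This ties the allowance to the time at which the primary outcome is measured, and it counts every patient missing from the primary analysis, whatever the reason.

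If the sponsor wishes to show the effect of per-protocol exclusions, it should state an assumed rate and label it as such.

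The cost is one sentence and a slightly less favourable stated figure. No patients are added, and neither the design nor the analysis changes.

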### Statistical analysis

The analysis of the per-protocol population will be considered the primary analysis. The differences between the CO UKA and RO UKA groups will be analysed by calculating the difference from baseline, per patient, and a two-sided confidence interval for the difference between the changes from baseline values will be calculated. This confidence interval will cover the true difference in the percentage change from baseline with a probability of 95%. The following statistical methods will be employed to analyse the data: descriptive statistics, independent *t* test, paired *t* test, analysis of variance, Fisher’s exact test, chi-square test, and graphical displays. Assumptions of normality will be tested with the D’Agostino test. Assumptions of homogeneity of variance will be tested with Levene’s test. If the distributional assumptions are (severely) violated, non-parametric techniques, such as Mann-Whitney’s test, will be employed. In the event that RO UKA is converted to CO UKA intraoperatively, analysis will be performed using the intention-to-treat population and the treatment actually received by the patients. Intraoperative conversion from RO UKA to CO UKA will be documented and presented and published as part of the study. The Bonferroni correction will be used to determine the level of significance due to multiple comparisons of secondary outcomes. Statistical significance is set at a *p* value < 0.05 for all analyses, and all statistical analysis will be performed using SPSS software version 26 (SPSS Inc., Chicago, IL, USA).

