## Methods/design

### Objectives

The primary objective of this study is to compare accuracy of implant positioning in CO UKA versus RO UKA. Accuracy of implant positioning will be assessed by measuring differences in the planned implant position on preoperative CT scan versus the achieved implant position on postoperative CT scan. The null hypothesis is that there is no difference in accuracy of implant positioning between CO UKA versus RO UKA.

The secondary objectives are to compare the following outcomes between the two treatment groups:
Limb alignmentSurgical efficiencyPostoperative functional rehabilitationFunctional outcomesQuality of lifeRange of motionMobilisation distanceResource use and cost effectivenessComplications

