### End of protocol treatment

Reasons for going off study protocol include:
Completion of last follow-up visit 2 years after surgeryPatient non-compliance or withdrawal (the reason for discontinuation will be recorded in the case report form)Intercurrent death

All patients included into this study are free to withdraw from the study at any time without compromise to their future treatment. On withdrawal, patients will revert to the standard follow-up regimen for routine (non-study) UKA at the study site. The end of study form will be completed and the reason for withdrawal documented. This form will also be completed if the patient is lost to follow-up or dies during the course of the study. Data to the point of discontinuation will be used for analysis.

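### The per-protocol analysis is primary in a test of difference, and the role of the analyses triggered by robotic-to-conventional conversion is not stated

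*Protocol article*

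**What the plan says.** All of this is in the Protocol article.

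- **Statistical analysis**, on the primary population: "The analysis of the per-protocol population will be considered the primary analysis".
- **Statistical analysis**, later in the same paragraph, for robotic (RO) operations converted to conventional (CO) during surgery: "analysis will be performed using the intention-to-treat population and the treatment actually received by the patients". The next sentence adds: "Intraoperative conversion from RO UKA to CO UKA will be documented and presented and published as part of the study".
- **Objectives**: "The null hypothesis is that there is no difference in accuracy of implant positioning between CO UKA versus RO UKA".
- **Sample size**: the calculation is two-tailed, with a "significance level of 5%, and an effect size of 0.5", from a 2° difference and an SD of 4°. No non-inferiority or equivalence margin appears.

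The word superiority is not used. It follows from the null hypothesis, the two-tailed test and the absence of a margin.

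**The concern.** In a test of difference, the comparison is protected by randomisation only if patients are analysed in the arm to which they were allocated. A per-protocol population is selected by what happens afterwards. Here the post-randomisation event that the article foresees is conversion in theatre. It is decided by a surgeon who necessarily knows the allocation, and it bears directly on the primary outcome, accuracy of implant position.

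If the harder robotic cases are the ones converted, dropping them flatters the RO arm. Moving them to CO does the same and also worsens the control arm. Either can produce an apparent accuracy gain where none exists.

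The second problem is one of specification. Once a conversion occurs, the article calls for two further analyses, and their standing against the declared primary analysis is left open. If they replace it, the primary population depends on an event during the trial and splits into two unranked analyses. If they accompany it, per-protocol stays primary. Neither reading gives a primary analysis by randomised arm.

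**Working it through.** **1. The plan's own figure.** Inputs from Sample size: difference 2°, SD 4°, so d = 2/4 = 0.5; two-sided 5%; power 80%. The two-sample t test gives 63.77, so 64 per arm and 128 in total, which matches the article. With 140 randomised and 10% lost, 140 × 0.9 = 126, or 63 per arm. Power at 63 per arm and d = 0.5 is 79.5%. The steps below use 63 per arm.

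**2. Bias if converted cases leave the RO arm.** This is a simulation under no true difference. Its assumptions, none of which the article supplies, are:

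- Absolute positioning errors are half-normal with scale 4° in both arms. Their SD is 4 × √(1 − 2/π) ≈ 2.4°, not the 4° of the sample-size section.
- Each RO case has a latent difficulty, correlated 0.3 to 0.7 with its error (correlation set on the normal scale). The most difficult cases are converted.
- Converted cases are dropped (per-protocol) or counted as CO (treatment received). Arms are compared with Welch's t test.

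| Conversions among 63 RO | Per-protocol: false RO advantage | Per-protocol: type I error | Treatment received: false RO advantage | Treatment received: type I error |
|---|---|---|---|---|
| 3 (3/63 = 4.8%) | 0.08–0.20° | 5.5–8.0% | 0.15–0.38° | 6.4–13.6% |
| 6 (6/63 = 9.5%) | 0.14–0.35° | 6.6–14.4% | 0.26–0.63° | 9.3–32.1% |

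Analysis by randomised arm keeps type I error at about 5% throughout, with bias near zero. Against the 2° design difference, the per-protocol bias is 0.08/2 = 4% to 0.20/2 = 10% with three conversions, and 0.14/2 = 7% to 0.35/2 = 17.5% with six.

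**3. Where the bias vanishes.**

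- Correlation zero (conversion unrelated to difficulty): type I error is 5.0–5.2% for both analyses at 1, 3 or 6 conversions.
- One conversion (1/63 = 1.6%): per-protocol bias is 0.03–0.07° and type I error 4.9–5.6%.

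**4. Sensitivity to the error distribution.** With normal errors of SD 4° and six conversions, type I error is 6.0–11.5% per-protocol and 8.5–25.6% by treatment received. The pattern is the same.

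**5. Cost of analysing by randomised arm.** Assume a fraction c of RO cases is converted and has the CO mean. The expected difference is then 2° × (1 − c), so d = 0.5 × (1 − c).

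| c | Expected difference | Power, 63 per arm | Evaluable N for 80% power |
|---|---|---|---|
| 0 | 2.0° | 79.5% | 128 |
| 5% | 1.9° | 75.3% | 142 |
| 10% | 1.8° | 70.7% | 158 |

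**The case against.** The strongest defence has four parts.

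- **An order is stated.** A reader might infer that the three analyses are unranked and that the most convenient may be chosen. The article does not support that: per-protocol is named primary. What is open is narrower, namely whether the conversion sentence overrides that choice and how the two conversion analyses rank against each other.
- **There is a safeguard.** When conversion occurs, the article requires an intention-to-treat analysis and publication of the conversions. A distorted primary result would therefore be visible. This stands, but visibility does not settle which analysis decides.
- **One-sided exclusion is not established.** A reader might infer that only RO patients can leave their arm. The definition of the per-protocol set is not shown and may sit in a fuller document. Conversion is named as a trigger for analyses, not as an exclusion rule, and CO patients could also be excluded. That converted cases drop out of the per-protocol set is a plausible assumption, not a stated rule.
- **The link to difficulty is assumed.** No reason for conversion is given. The Adverse events section contemplates problems with the robotic device, which need not follow case difficulty, and without that link there is no bias.

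Two further inferences should be resisted. The sentence under End of protocol treatment, "Data to the point of discontinuation will be used for analysis", concerns withdrawal from follow-up and adds nothing about conversion. The largest type I error in the table, 32.1%, belongs to the treatment-received analysis in the most extreme scenario, and the article does not name that analysis as primary.

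An unseen analysis plan does not remove the point. One that follows the article inherits the problem, and one that makes intention-to-treat primary contradicts it.

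**Conclusion.** The concern holds in this limited form. The article fixes a per-protocol primary analysis for a test of difference and does not say what role the two conversion-triggered analyses play. This rests on the text alone and does not depend on the simulation.

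The size of any bias does depend on assumptions. If converted cases leave the RO arm and conversion goes with difficulty, per-protocol type I error is modestly raised at three conversions and can reach about 14% at six. With rare or unrelated conversions the effect is negligible. Since the article gives neither rate nor cause, the figures are scenarios and not predictions. It would be worth settling in any case, because the population that decides the primary endpoint should be fixed before results by arm are seen.

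**What to change.** Replace the sentence naming the primary population with wording such as: *The primary analysis includes all randomised patients with a postoperative CT, analysed in the arm to which they were randomised, including intraoperative conversions in either direction; per-protocol and treatment-received analyses are supportive.* Delete the conditional switch on conversion.

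Two additions are needed:

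- **State in advance which preoperative plan defines positioning error for a converted patient.** Under Blinding, each technique takes only its own manufacturer's implant. Under Preoperative imaging, RO plans are made in the robotic software, while CO targets start from the manufacturer's manual. A converted patient would have a plan for one implant and receive another.
- **Report patients without a postoperative CT by arm.** Restricting to those scanned is not a full intention-to-treat analysis.

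The cost is a text amendment, a measurement rule for converted cases, and some power if conversions occur: 79.5% falls to 75.3% at 5% conversion and 70.7% at 10%, if converted cases have the CO mean.

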### Outcomes

All study patients will undergo review by two blinded observers (one orthopaedic registrar and one clinical research fellow) at 6 weeks, 6 months, 1 year, and 2 years following surgery. During these follow-up times, predefined clinical outcomes will be recorded by these observers using case report forms (CRFs). In addition, three independent observers (clinical research fellows) will collect radiological outcomes. It is not possible to blind observers recording radiological outcomes as different implant designs will be used within each treatment group. However, the three observers will independently calculate the accuracy of femoral and tibial implant positioning in each patient, and interobserver agreement for all radiological outcomes will be investigated using interclass correlation coefficients.

The following outcomes will be recorded in all study patients:
Accuracy of achieving the planned implant positioning as assessed using CT scans performed postoperatively at 6 weeks.Operating time (minutes)Time to hospital discharge (hours)Analgesia requirements during inpatient admission and postoperatively at 6 weeks, 6 months, 1 year, and 2 yearsPatient-reported outcome measures including Oxford knee score (OKS) and short form (SF-12), Western Ontario and McMaster Universities Arthritis Index (WOMAC), Knee injury and Osteoarthritis Outcome Score (KOOS), and University College Hospital (UCH) functional score during inpatient admission and postoperatively at 6 weeks, 6 months, 1 year, and 2 years.Health-related quality of life as measured using European Quality of Life questionnaire with 5 dimensions for adults (EQ-5D) preoperatively and postoperatively at 6 weeks, 6 months, 1 year, and 2 yearsMobilisation distance (metres) and use of mobility aids during inpatient admission and postoperatively at 6 weeks, 6 months, 1 year, and 2 yearsRange of movement (degrees) in the knee joint during inpatient admission and postoperatively at 6 weeks, 6 months, 1 year, and 2 yearsResource use and cost-effectiveness including comparisons between the two treatment groups relating to: Operating time, theatre efficiency, equipment and sterilisation costs, analgesia requirements, inpatient rehabilitation, time to discharge, outpatient follow-up, additional imaging costs, and need for further surgery.Complications

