All patients will undergo preoperative and postoperative CT scans of the knee joint using a standardised protocol within a dedicated research scanner in the study hospital. The CT scans will be uploaded in DICOM (Digital Imaging and Communication in Medicine) format and then loaded onto Mimics software (Materialise) to calculate the accuracy of implant positioning. Accuracy of implant positioning will be assessed by comparing differences in the target values in the preoperative plan to the achieved values in the postoperative scan. These outcomes will be used to calculate root mean square errors values for accuracy of femoral and tibial component positioning within the coronal, sagittal, and axial planes as described by Bell et al. [4]. The posterior condylar offset ratio (PCOR) and posterior tibial slope will be assessed using the methods described by Gaudiani et al. and Johal et al. respectively [13, 23].

The WOMAC, OKS, SF-12, EQ-5D, and KOOS are validated tools for the clinical assessment of patients after knee arthroplasty [11, 12, 17, 22, 39]. In addition, the observers will calculate the UCH knee score to assess overall, pain, function, and mobility [19]. This will help to overcome any potential ceiling effect with the OKS and WOMAC and facilitate further subgroup analysis in patients with high functional demands [19]. Each of these clinician- and patient-reported scores will be collected preoperatively at the time of consenting to the study and also postoperatively at 6 weeks, 6 months, 1 year, and 2 years after surgery.

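### The general change-from-baseline analysis carries a false coverage statement about percentage change, does not fit the primary CT endpoint, and is less efficient than ANCOVA for the scores

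*Protocol article*

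**What the plan says.** All references are to the protocol article.

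- **Statistical analysis, general rule.** Differences between the groups "will be analysed by calculating the difference from baseline, per patient", with a two-sided interval for the between-group difference in those changes. No outcome is exempted.
- **Statistical analysis, next sentence.** "This confidence interval will cover the true difference in the percentage change from baseline with a probability of 95" per cent.
- **Statistical analysis, methods list.** Independent and paired t tests, then "analysis of variance, Fisher’s exact test, chi-square test, and graphical displays", with Mann-Whitney as the fallback. No baseline-adjusted model is named, and no test is tied to a particular outcome.
- **Objectives.** Accuracy, the primary outcome, is assessed by "measuring differences in the planned implant position on preoperative CT scan versus the achieved implant position on postoperative CT scan".
- **Outcomes.** The timing is "Accuracy of achieving the planned implant positioning as assessed using CT scans performed postoperatively at 6 weeks", and the summary is "root mean square errors values for accuracy of femoral and tibial component positioning within the coronal, sagittal, and axial planes".
- **Outcomes, clinician- and patient-reported scores.** These "scores will be collected preoperatively at the time of consenting to the study" and again at 6 weeks, 6 months, 1 year and 2 years. EQ-5D is also listed as measured preoperatively.
- **Sample size.** A two-tailed, two-sample t test on femoral sagittal positioning, with difference 2°, SD 4°, 80% power and 5% significance, gives 128 evaluable patients.

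**The concern.** There are three separate faults in a few lines of text.

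First, an interval constructed for a difference in changes is said to have 95% coverage for a difference in percentage changes. The two have different units and generally different true values.

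Second, the rule covers every outcome, but the primary one has no baseline. There is no implant before surgery, and the plan is a target rather than a measurement of the patient's starting state. Read literally, the analysis section therefore prescribes for the primary endpoint something that cannot be computed, and it differs from the test on which the trial was sized. That leaves the primary estimand open to choice after the data are seen: signed or absolute deviation, degrees or percentage.

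Third, the scores do have a baseline, recorded at consent and so before randomisation, but the stated change-score comparison does not use it as well as it could. These are secondary outcomes subject to a Bonferroni correction, so precision matters.

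**Working it through.** **1. The plan's own figure.** The standardised effect is 2/4 = 0.5. At 80% power and two-sided 5%, the t distribution gives 63.77, so 64 per arm and 128 in total. The stated figure reproduces. It comes from a two-group comparison of positioning with no baseline term.

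**2. The two interval sentences.** Write Y0 for baseline and Y1 for follow-up. The interval is for the between-group difference in mean (Y1 − Y0). The coverage sentence concerns the between-group difference in mean 100(Y1 − Y0)/Y0. Dividing each patient's change by that patient's own Y0 changes both units and weighting, so an interval for the first has no stated coverage for the second. The second is also undefined at Y0 = 0 and unstable near it.

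**3. Can the plan serve as the baseline for the primary endpoint?**

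- *As a percentage.* The percentage error is 100 × error/target. A 2° error is 20% of a 10° target, 40% of 5° and 400% of 0.5°, and is undefined at 0° (illustrative targets).
- *As a signed change, achieved minus planned.* Assume both arms are centred on plan, with error SDs of 4° and 2° and 64 patients per arm. In 20,000 simulated trials, a t test on signed deviation rejected in 5.1%, which is the nominal error rate. A t test on absolute deviation rejected in 99.9%. A mean signed deviation can therefore miss a difference in precision entirely.

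The root mean square error in the Outcomes section shows that magnitude is what is wanted.

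**4. Efficiency for the scores.** Set the variance to 1 at baseline and at follow-up, and let rho be the correlation between them. The documents give no rho, so a range is assumed.

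- Follow-up value alone: variance 1
- Change score: 2(1 − rho)
- ANCOVA: 1 − rho²
- ANCOVA/change: (1 − rho)(1 + rho) / [2(1 − rho)] = (1 + rho)/2

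Power below is for an illustrative 0.5 SD effect, 64 per arm, two-sided 0.05, before any Bonferroni correction.

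| rho | Change variance | ANCOVA variance | Ratio | Power, change | Power, ANCOVA |
|---|---|---|---|---|---|
| 0.2 | 1.60 | 0.96 | 0.60 | 60.2% | 81.7% |
| 0.3 | 1.40 | 0.91 | 0.65 | 66.0% | 83.7% |
| 0.5 | 1.00 | 0.75 | 0.75 | 80.1% | 90.0% |
| 0.7 | 0.60 | 0.51 | 0.85 | 95.2% | 97.6% |

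Follow-up alone has 80.1% power throughout. It beats the change score below rho 0.5, ties at 0.5 and loses above. ANCOVA beats the change score at every rho below 1. The one degree of freedom it spends is ignored, which is negligible at this size.

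**The case against.** The strongest reply is that the general rule was probably written for the scores, and that a usable test for the primary endpoint is named twice: the two-sample t test in the Sample size section and the independent t test in the methods list. This stands in part. A reader might infer that the primary outcome cannot be analysed at all, and the documents do not support that. The fault is that the rule is unrestricted and the applicable test is never assigned to the primary endpoint.

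On efficiency, unadjusted change scores are unbiased under randomisation, and covariate adjustment is commonly left to a full protocol or analysis plan that is not shown here. That also stands: the absence of ANCOVA from a condensed article is not an error. What can be addressed is the change-score analysis that the article does state, for which a more precise alternative exists using data already collected.

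Two stronger readings should be resisted. One is that change scores are the least efficient option. Against follow-up alone this holds only for rho below 0.5, and rho is unknown. The other is that the functional comparisons have the powers tabulated above. The documents give no effect size, SD or power target for any score, the 0.5 belongs to femoral sagittal positioning, and the Bonferroni correction would lower every figure.

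None of this reconciles the two interval sentences. No unseen analysis plan can make both true as published.

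**Conclusion.** The coverage sentence is wrong as written and needs correcting, whatever a separate analysis plan says. The unrestricted change-from-baseline rule does not fit the primary endpoint, operating time or time to discharge, and treating the plan as a baseline does not rescue it. The primary endpoint remains analysable, but its analysis should be stated where the analyses are stated.

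The efficiency point is a free improvement rather than an error. ANCOVA has 15% to 40% less variance than a change score for rho from 0.7 down to 0.2, with the gain shrinking as rho rises. This rests on equal variances at baseline and follow-up and on an assumed rho. The simulation in step 3 rests on assumed error SDs and shows what can go wrong, not what will happen in this trial.

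**What to change.** 1. Delete the sentence on percentage change.
2. Limit baseline-based analysis to outcomes with a preoperative value. For operating time and time to discharge, name a direct two-group comparison.
3. State the primary analysis as a between-group comparison, with 95% confidence interval, of the magnitude of planned-to-achieved deviation at 6 weeks for the femoral component in the sagittal plane, on which the trial is sized. Absolute or squared deviation per patient would be consistent with the root mean square error summary: for a single measurement, the root of the squared error is the absolute error. Say which is used, and that the 2° and 4° refer to it.
4. Analyse the clinician- and patient-reported scores and EQ-5D by ANCOVA at each visit, or by one repeated-measures model over 6 weeks to 2 years, adjusted for the preoperative value. Report adjusted mean differences.

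The cost is wording and standard models. No new data are needed, and the 128 evaluable patients stand at the plan's standardised effect of 0.5.
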